## Abstract

**Background:**

Despite record rates of childhood obesity, effective evidence-based treatments remain elusive. While prolonged tertiary specialist clinical input has some individual impact, these services are only available to very few children. Effective treatments that are easily accessible for all overweight and obese children in the community are urgently required. General practitioners are logical care providers for obese children but high-quality trials indicate that, even with substantial training and support, general practitioner care alone will not suffice to improve body mass index (BMI) trajectories. HopSCOTCH (the Shared Care Obesity Trial in Children) will determine whether a shared-care model, in which paediatric obesity specialists co-manage obesity with general practitioners, can improve adiposity in obese children.

**Design:**

Randomised controlled trial nested within a cross-sectional BMI survey conducted across 22 general practices in Melbourne, Australia.

**Participants:**

Children aged 3–10 years identified as obese by Centers for Disease Control criteria at their family practice, and randomised to either a shared-care intervention or usual care.

**Intervention:**

A single multidisciplinary obesity clinic appointment at Melbourne’s Royal Children’s Hospital, followed by regular appointments with the child’s general practitioner over a 12 month period. To support both specialist and general practice consultations, web-based shared-care software was developed to record assessment, set goals and actions, provide information to caregivers, facilitate communication between the two professional groups, and jointly track progress.

**Outcomes:**

*Primary* - change in BMI z-score. *Secondary -* change in percentage fat and waist circumference; health status, body satisfaction and global self-worth.

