## Aims and hypothesises

The **aim of the HopSCOTCH trial** is to develop, implement and trial an innovative shared-care approach to manage childhood obesity. We will compare outcomes for 3–10 year old obese children randomised to a shared-care model (general practitioners working with paediatric obesity specialist, consisting of a paediatrician and dietician - ‘intervention’ group) with outcomes for those receiving usual patient-driven primary care (‘control’ group).

We **hypothesise** that:

1. Compared to the control group, the intervention children will demonstrate better outcomes at 15 months in terms of lower:

i) Relative BMI, measured as a z-score (primary outcome)

ii) Percentage body fat

iii) Waist circumference

2. Compared to the control group, the intervention children will not show evidence of harm (ie poorer health status, body satisfaction, or global self-worth) at 15 months.

3. The intervention will be acceptable and feasible to (i) parents, (ii) general practitioners, (iii) general practice staff, and (iv) the obesity specialists.

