### Obesity specialist consultation

The shared-care intervention involved each family (at a minimum the index child and one parent/guardian) attending a single one-hour session at Melbourne’s Royal Children’s Hospital, where they saw the obesity specialist team comprising a paediatrician and a paediatric dietician who specialise in childhood obesity and weight management. Prior to the appointment, researchers extracted clinically-relevant information about the child and family from the baseline questionnaire, including family history, medical history, daily diet, physical activity and sedentary activities, and scored multi-item scales (see Additional file 1). These data were entered into a summary, with abnormal values flagged, in order to both save time on history-taking and to provide additional information that would not normally be available during a single first clinical consultation (see completed example Additional file 1). This allowed the team to devote more consultation time exploring lifestyle modification, rather than primarily information gathering.

At the appointment, a researcher first measured the child’s height, weight and percentage of truncal fat. The paediatrician then interviewed the child and family, taking a clinical history and examining the child using a standard protocol to identify possible causes and co-morbidities of obesity. The dietician then undertook a detailed dietary history and outlined general principles of healthy eating, offering targeted advice based on the child and family’s eating patterns. Physical and sedentary activities were assessed and, together, the paediatrician and dietician then discussed the lifestyle changes required that would most likely assist in successful weight management for the child. This advice focussed on family change and support, in accordance with research showing beneficial results to the child when the parents are involved [32], and is consistent with current recommendations that, for most obese children, BMI reduction is best achieved by maintaining, rather than losing, weight as the child grows [33]. Details of the specialist consultation, including the clinical summary and pathology results (if applicable) and an initial care plan, were then entered into the shared-care software.

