**Primary Outcome**				
Body Mass Index (kg/m^2^)	**•**	**•**	Portable rigid stadiometer (model IP0955, Invicta, Leicester, UK); measured Calibrated digital scale (model TITHD646, Tanita, Toyko, Japan); measured	Height is measured twice and the average used; if the values differ by >0.5 cm a third measurement is taken and the average of the two closest values used. Weight, while wearing light clothing, is measured once at baseline, and measured twice at outcome. Average weight used at outcome; if the values differ by ≥0.2 kg a third measure was taken and average of the two closest values used. BMI is calculated as weight (kg)/(height (m)2). BMI z-score is calculated according to the US Centers for Disease Control (CDC) reference values [28], using the Stata ‘zanthro’ function.

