**Secondary Outcomes**				
Waist circumference		**•**	Lufkin Executive Steel Tape (W606PM); measured	Average of two waist measurements; if they differ by ≥1 cm, a third measurement is taken and the mean of the two closest used.
Body fat (%)		**•**	Tanita Digital Body Composition Monitor (BC-351)[37]; measured	Average of two body percentage fat measurements.
Blood pressure/ heart rate		**•**	Welch Allyn ProBP3400; measured	Three blood pressure/heart rate readings are taken at least two minutes apart on the right arm with the child sitting; the average of the two closest readings is used.
Nutrition		**•**	4 day food diary; parent report	Parents report child’s consumption of each of 17 food and drink items (0, 1, 2, >2 times) for two weekdays and two weekend days. Dichotomous (“yes” v “no”) variables are derived for five “healthy behaviours” (high fruit, vegetables, and water; low fatty/sugary foods and non-diet sweet drinks) for each day. The number of healthy behaviours per day are summed to give a score between 0 and 5 (higher score indicating more healthy behaviour).
Physical activity		**•**	Actical Accelerometer (Mini Mitter); measured	Worn for 7 full days; ≥5 valid days required. Valid days have ≥10 hours of non-missing data between 6 am-11 pm. Missing data are segments with ≥20 minutes of consecutive “0” counts, or counts >0 that are constant for ≥10 minutes. Outcomes across all valid days: mean activity counts/min, and % time spent in moderate to vigorous physical activity.
Health status	**•**	**•**	Paediatric quality of life inventory (PedsQL 4.0); self report and parent-proxy versions [38]	Parent-completed 23-item scale that yields total, physical summary, and psychosocial summary scores, each with a possible range of 0–100 (100 = best possible health); quantitative variable.
Body dissatisfaction		**•**	Body figure perception questionnaire; self report [39]	Child picture scale of 1–7 (1 = underweight, 7 = obese) from which child picks perceived and ideal selves. “Perceived” minus “Ideal” self yields a discrepancy index, with positive and negatives scores representing desires to be thinner and fatter, respectively.

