### Data Analysis

Analyses will be by ‘intention to treat’ at the level of the individual child. Linear regression will be used to compare quantitative outcomes between the trial groups adjusting for confounders and baseline measures of the outcomes where these are available, using an analysis of covariance approach. Logistic regression will be used to compare dichotomous outcomes.

Confounders selected *a priori* for multivariable models will include child sex, age at randomisation, and family socioeconomic status, which will be assigned according to postal code of residence using the Index of Relative Socioeconomic Disadvantage (mean 1000, s.d. 100) from the Australian Bureau of Statistics census-based Socio-Economic Indexes for Areas (SEIFA) [36].

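### The abstract names change in percentage fat and waist circumference, but neither has a baseline, and the covariate rule leaves both without the baseline BMI z-score already held for every child

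*Protocol article*

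**What the plan says.** The protocol article describes these two outcomes in several places.

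- **Abstract, Outcomes:** the secondary outcomes begin with "change in percentage fat and waist circumference".
- **Aims and hypothesises, hypothesis 1:** "the intervention children will demonstrate better outcomes at 15 months in terms of lower" BMI z-score, percentage body fat and waist circumference. This is a level at 15 months, not a change.
- **Table 1, secondary outcomes:** waist and body fat are marked at the outcome time point only. For waist the derivation is "Average of two waist measurements; if they differ by ≥1 cm, a third measurement is taken and the mean of the two closest used", and for fat "Average of two body percentage fat measurements". Neither row mentions a baseline reading.
- **Table 1, primary outcome:** BMI is marked at both time points. Weight "is measured once at baseline, and measured twice at outcome", and "BMI z-score is calculated according to the US Centers for Disease Control (CDC) reference values".
- **Recruitment of children:** before enrolment, children are weighed and their height is taken at the practice. Consent and the parent questionnaire then go by mail.
- **Obesity specialist consultation:** at the clinic visit "a researcher first measured the child’s height, weight and percentage of truncal fat". The Control arm section says that control children were not offered this visit.
- **Data Analysis:** linear regression adjusts for confounders and for "baseline measures of the outcomes where these are available". The confounders chosen in advance are sex, age at randomisation and the SEIFA disadvantage index.

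**The concern.** Two things follow from reading these sections together.

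First, the abstract and the hypotheses define the same two outcomes differently, and only the hypotheses' version can be produced from the measurements listed. A reader who later compares the results with the abstract would look for a change score that cannot exist.

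Second, the adjustment rule depends on each outcome having its own baseline. Waist and percentage fat have none, so the rule gives them sex, age and SEIFA and nothing that reflects how obese the child was at entry. A measure of that is held for everyone, because a BMI at or above the 95th percentile was an entry condition. Randomisation is stratified by general practitioner only, so nothing in the design balances baseline adiposity between arms. Hypotheses 1(ii) and 1(iii) would be tested with more residual noise than necessary, and any chance difference in starting adiposity would pass uncorrected into the estimates.

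**Working it through.** **Can change be computed?** Change needs the same quantity measured before randomisation in both arms.

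| Quantity | Before randomisation | After randomisation |
|---|---|---|
| Weight, height, BMI z-score | Yes, all children | 15 months, both arms |
| Waist circumference | None described | 15 months, both arms |
| Body fat (%) | None described | 15 months, both arms |
| Truncal fat (%) | None described | Clinic visit, intervention arm only |

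The truncal fat reading comes after randomisation, exists in one arm, and is labelled as a different quantity from the body fat in Table 1. It cannot serve as a trial baseline. Change in waist or percentage fat therefore cannot be formed; the 15-month level can.

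**The plan's own figure.** No sample size or power is stated for waist or percentage fat. The target of 172 in the Sample size section concerns BMI z-score and has no stated SD. Back-solving with a difference of 0.3, 80% power, two-sided 5% and equal arms: 172 × 0.9 = 154.8, or about 77 per arm, and SD = 0.3 / 2.802 × √(77/2) ≈ 0.66. The point here does not depend on that figure.

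**What the covariate is worth.** Let r be the correlation of baseline BMI z-score with the 15-month outcome, after sex, age and SEIFA. The article does not give r, so a range is used. One extra covariate costs one degree of freedom, which is ignored.

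- Ratio of standard errors, with to without: √(1 − r²)
- Equivalent multiplier on sample size: 1 / (1 − r²)

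| Assumed r | 1 − r² | SE ratio | Fall in SE | Equivalent extra children |
|---|---|---|---|---|
| 0.3 | 0.91 | 0.954 | 5% | 10% |
| 0.5 | 0.75 | 0.866 | 13% | 33% |
| 0.7 | 0.51 | 0.714 | 29% | 96% |

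**Detectable difference.** At 80% power and two-sided 5%, in units of the outcome's SD, with n children per arm: (1.960 + 0.842) × √(2(1 − r²)/n). Two sizes are shown, because the Sample size section aims for 172 and the Participants section gives 120. Each is reduced by the planned 10% loss: 172 × 0.9 = 154.8 (n = 77.4) and 120 × 0.9 = 108 (n = 54).

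| Assumed r | 154.8 evaluable | 108 evaluable |
|---|---|---|
| 0 (no covariate) | 0.45 SD | 0.54 SD |
| 0.3 | 0.43 SD | 0.51 SD |
| 0.5 | 0.39 SD | 0.47 SD |
| 0.7 | 0.32 SD | 0.39 SD |

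**Chance imbalance.** The between-arm difference in mean baseline BMI z-score has a standard error of √(2/n) in its own SD units. With n = 54 this is √(2/54) = 0.19. Unadjusted, an imbalance of that size moves the outcome estimate by r × 0.19, which is about 0.10 SD at r = 0.5. This is the same gain seen from another side, not an additional one.

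**The case against.** The strongest reply is that the mismatch is one loose word in an abstract. Hypothesis 1 already frames both outcomes as levels at 15 months, the Measures and training section puts all outcome measurement at 15 months, and the Data Analysis section foresees outcomes without a baseline. This stands. A reader might infer that a secondary outcome is lost or that hypotheses 1(ii) and 1(iii) cannot be tested. The article does not support that: the analysis can be run in full, and the correction is to the abstract's wording.

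A reader might also infer that the clinic truncal fat reading would be used as a baseline, which would treat the arms asymmetrically. No section proposes this, and the reading is not among the Table 1 outcomes. It matters here only because it does not fill the gap.

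The marks in Table 1 are not wholly reliable: the parent BMI row carries only an outcome mark although its text refers to baseline values. But that row names its baseline source, which is parent report. The waist and fat rows name none, and the recruitment text agrees with the empty cells.

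On the covariate, it can be said that the confounder list is not expressly closed, that model detail may sit in an analysis plan that is not shown, and that adjusting for an outcome's own baseline where one exists is standard. All this is fair, and it limits the weight of the point. It does not remove it, because the article states a covariate rule chosen in advance, and that rule as written gives these two outcomes no adiposity term.

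Finally, the gain rests on an assumed r. Every child is at or above the 95th percentile, and this restriction of range may lower the correlation. Quoting only the upper part of the range would overstate the benefit, so values down to 0.3 are shown.

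**Conclusion.** The point holds as a wording inconsistency and an avoidable loss of precision in two secondary outcomes. The abstract's change in percentage fat and waist circumference cannot be computed from the measurements described, and only the 15-month level in hypothesis 1 can be analysed. Under the stated rule both outcomes are adjusted for sex, age and SEIFA only, while baseline BMI z-score is available for every randomised child.

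A reader might take the missing covariate to mean a biased comparison. It does not: randomisation keeps the comparison unbiased without it. The gain is a standard error lower by about 5% to 29%, equivalent to about 10% to 96% more children, for an assumed residual correlation of 0.3 to 0.7. The article does not give that correlation, and it may lie toward the low end in a wholly obese sample. The primary outcome is not affected, because BMI has its own baseline.

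**What to change.** 1. In the abstract, delete the word change for percentage fat and waist circumference, and describe both as values at 15 months compared between arms, as in hypothesis 1.
2. In the Data Analysis section, state that the waist and percentage fat models adjust for baseline BMI z-score in addition to sex, age at randomisation and SEIFA.

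The cost is two short edits and one covariate already held. No new measurement, visit or child is needed. The covariate should be fixed before outcome data are examined by arm, so that its choice cannot depend on the results.

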**Discussion:**

This will be the first efficacy trial of a general-practitioner based, shared-care model of childhood obesity management. If effective, it could greatly improve access to care for obese children.

**Trial Registration:**

Australian New Zealand Clinical Trials Registry ACTRN12608000055303

## Background

Despite recent indications that the upward trend in childhood obesity is plateauing, its prevalence remains at historically high levels [1]. Although childhood obesity affects around 6% (approximately 200,000) of all Australian children, very few of them receive treatment from their general practitioner or paediatrician [2,3]. Effective evidence-based treatments remain scarce and are generally only available to small proportions of seriously obese children through tertiary care settings. Whilst prevention must ultimately be the main goal, there are already a large number of obese children who urgently require effective treatment if the consequences for their adult health – such as heart disease and diabetes, psychological morbidity, and massive excess health care costs – are to be avoided.

So far, the only healthcare setting that is consistently documented to reproducibly improve the body composition and health of obese children is the specialist obesity clinic, generally involving lifestyle advice, motivation and feedback provided by a multidisciplinary team over a year or more. Mean reductions in body mass index (BMI) z-score sustained to at least 12 months are typically around 0.3 [4]; approximately 85% of children typically achieve at least some overall reduction in BMI z-score although only around 30% achieve the reduction of ≥0.5 [4,5] that equates to definite reductions in fat mass [6] and quantifiable improvements in risk factors for heart disease and diabetes [4,7]. Unfortunately, although intervention appears more successful for younger children, the caseload of specialist obesity clinics is often typically skewed towards adolescents with significant psychological, social and family dysfunction for whom treatment is less effective [4]. Furthermore, such clinics are inaccessible to almost all children. By our estimation the nine obesity clinics in children’s hospitals around Australia could see, at most, around 0.05% of affected Australian children each year, and it seems likely that other countries would have similar situations.

Therefore, as the only universally-accessible healthcare service available throughout childhood, general practice might seem the obvious healthcare setting to support the improvement, achievement and maintenance of healthy weight in children who are already overweight or obese. However, trials of obesity approaches in which treatment is initiated and carried out solely by general practitioners, with or without allied health services, have been extraordinarily disappointing to date both for adults [8] and children [9-12]. A new approach is therefore needed to augment the treatment of childhood obesity in primary care.

Nonetheless, there remain good reasons for optimism when considering general practice as a mode for the successful management of paediatric obesity. Firstly, this is where the majority of overweight/obese children present. In a study of 3000 Victorian primary school children, parents reported that 55% of overweight children had attended a GP once or twice in the preceding six months, and 22% three or more times [13]. In two subsequent randomised controlled trials, we have also shown that: (1) general practitioners can and do take up training to offer a series of structured consultations using strategies for family lifestyle change, (2) that they are able to systematically identify children in the overweight and obese categories, (3) that families are willing for their children to be screened for BMI and not only engage, but persist, with their general practitioner, and (4) that this approach does not appear to be harmful for overweight or mildly obese children [10,14]. GPs are very clear that the management of childhood obesity falls within their role [15] and with training they can feel comfort and competent in this area [16].

The literature on shared-care approaches incorporating primary and specialist partnerships is relatively limited but encouraging in achieving similar [17,18] or better [19] disease outcomes with important ancillary outcomes such as increased satisfaction [20] and reduced waiting times [21]. For instance, an adult rheumatoid arthritis trial demonstrated higher quality-adjusted life-years for the shared-care than the aggressive arm [18], while a shared-care intervention for patients newly diagnosed with cancer increased general practitioner contact and positively influenced patients’ attitudes toward the healthcare system [17]; in neither trial was the disease outcome poorer in the shared-care arm. However, few shared-care trials have focused on children, and none on childhood obesity.

Given the potential benefits of health information technology to general practice [22], the Australian government has prioritised its use and value [23] with the result that, by 2005, 80% had broadband access and nearly 90% used a computer for clinical purposes [24], and is most likely close to 100% as of 2011. Some health information technology features are already nearly universally (eg prescribing) or frequently (eg accessing patient educational material) used, but far fewer general practitioners (<20%) are accessing computerised clinical information or using online decision support during consultations [24]. It is clear that e-health has both promise and limitations [25] and that the potential will not be actualised without carefully designing e-health initiatives into the primary care process. Health information technology could present an excellent mechanism to enhance shared-care models.

The HopSCOTCH (Shared Care Obesity Trial in Children) randomised trial is the first to our knowledge to study the efficacy of a general-practitioner based, shared-care model in reducing obesity in children – a population relatively underserved by evidence-based approaches [26]. The intervention needs to be developed in such a way that it could be widely implemented with consistency and sustainability, but with relatively little training. Underpinning this would be a very practical software platform that would provide standalone guidance and information to GPs while also enhancing primary-specialty care partnerships. The software would also support continuing practice improvement activities and the individual practitioner feedback that has proved useful in many fields [27]. Essentially, we hope to replicate the effectiveness of the specialty obesity clinic in the general practice setting, with attention to feasibility, sustainability and a wider and more systematic availability.

